### Enhanced Standard of Care

Given that existing MM models focus on vertical HIV transmission and HIV prevention and treatment, and our primary aim is to understand how inclusion of alcohol reduction strategies reduces alcohol use and improves adoption of ART/PrEP use, we will use enhanced SOC with the same time frame for the intervention (eg, two to three sessions during antenatal and two to three sessions during postpartum periods). This will consist of educational counseling delivered by peers (mentor mothers) on HIV risk, partner testing modalities, and PrEP/ART urine assay testing, followed by real-time in-clinic adherence counseling delivered privately (one on one) by mentor mothers (separate from intervention mentor mothers to avoid contamination), all coinciding with routine ANC visits when possible.

Benefits of the study include counseling and support from lay counselors (in SOC) and mentor mothers (in the intervention) to address alcohol use and HIV prevention and care. Risks include unintended disclosure of alcohol use or HIV status by providers or staff and potential breaches of confidentiality that could cause social harms, including IPV. We will train staff and providers to ensure they are aware of these risks and do not share details of participants’ status outside of the study. We will monitor all social and other study harms throughout the study through regular surveys and review of medical records.

### RCT Inclusion Criteria

Women who are ≥16 years old, with a confirmed pregnancy; who report alcohol use during pregnancy (in the past 2 months); who live within 20 km of the study facility; and who are able and willing to consent to study participation are eligible to participate.

One trained research assistant based at the ANC clinic will screen and obtain informed consent from PLW during their routine ANC visits using a set script for screening participants. We have received a waiver of parental consent for adolescents aged 16 and 17 years.

We will randomize the enrolled participants who have provided informed consent to the MM+ intervention or to enhanced HIV attention control in a 1:1 ratio. Randomization will be performed immediately following enrollment using dynamic permuted blocks with REDCap randomization sequentially. Trained researchers will not have access to the random allocation sequence. The intervention is nonblinded.

All study procedures will be in a private space in the Saldanha Bay municipality clinics, including screening, review, and signing of consent forms, surveys, and other procedures. This space will be dedicated research space given to the Human Science Research Council (HSRC) and FARR teams. We will ask pregnant women who may be interested in the study to see the study staff (in the study room) at the end of their visits or to get an appointment for another day to return to the clinic for study enrollment (if eligible).

### Analysis Plan

#### Outcomes

The implementation outcomes include feasibility (provider, organizational, and participant feedback), acceptability (number of sessions attended, feedback on content), and fidelity to study SOPs on MM+. The safety outcomes include IPV and pregnancy and birth outcomes (including preterm birth, birth weight, and miscarriage or stillbirth and infant survival) [48,49].

#### Power Calculations

We calculated power based on a 20% or more reduction in alcohol use in the intervention arm compared to no reduction (or minimal <5% reduction) in the control group. By enrolling 100 pregnant women (n=50, 50%, per arm), our study will be adequately powered at >80% for all primary effectiveness outcomes of feasibility and reduction in alcohol use. In qualitative work, the sample size is determined by the number of interviews expected with a specific population to reach thematic saturation [50,51].

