Despite these risks, community-informed interventions targeting both HIV and alcohol use among PLW are lacking. The few existing brief interventions targeting alcohol use during pregnancy have shown limited effectiveness, in part due to short follow-up periods and the absence of biomarker validation [18,19]. Integrating peer mentor mothers into existing care structures is one promising evidence-based approach that has improved maternal health outcomes and reduced vertical HIV transmission in South Africa [20,21]. The existing Mentor Mother (MM) intervention, implemented by peer mothers to mothers, leverages task shifting, where positive deviant peer mothers provide counseling and support, typically through home-based delivery. The prior models have focused mostly on prevention of vertical HIV transmission but do not include any messaging on alcohol or substance use reduction. The previous interventions have been successfully adapted to address broader maternal-child health outcomes in Africa and have shown promise in reducing alcohol use [22]. However, alcohol has never been the primary focus of MM intervention content. Guided by ADAPT-ITT (assessment, decision, adaptation, production, topical experts, integration, training, testing), a framework developed to systematically adapt evidence-based HIV interventions, our study seeks to adapt the MM approach to reduce alcohol use and improve HIV prevention and treatment outcomes among PLW in South Africa [23].

Brief interventions for alcohol use in pregnancy have shown limited effectiveness. Although interventions such as the Philani Program Plus (an MM model) have shown reduction in alcohol use over extended periods, achieving early abstinence remains challenging [24]. Our study aims to bridge these gaps by integrating motivational interviewing (MI) techniques to assist with reduction in alcohol or other substance use through peers with lived experience of being pregnant and reducing or stopping alcohol use during pregnancy and breastfeeding.

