Acceptability and uptake of and satisfaction with the intervention	Evaluate the organizational, provider, and PLW^c^ acceptability of the intervention, including the number and percentage of sessions attended and IDI^d^ feedback following the sessions. Success would be >80% of sessions attended with very good/good feedback postsessions.	Mixed methods	Postimplementation mixed methods: 6-month survey (all participants), followed by IDIs with 20 providers and 20 participants
Fidelity to training assessment	Evaluate sessions (20% recorded and reviewed by the principal investigator) and fidelity to training using a checklist of key parameters. Success would be >80% of sessions supervised following training SOPs^e^.	Monitoring forms: comparison of SOPs and audio-recorded MM+^f^ sessions	Postimplementation mixed methods: 6-month survey (all participants), followed by IDIs in 20 providers and 20 participants
Feasibility of the intervention	Evaluate organizational, provider, and PLW views on the feasibility and scalability of the implementation of the intervention.	Mixed methods	Postimplementation mixed methods: 6-month survey (all participants), followed by IDIs in 20 providers and 20 participants

^a^PrEP: pre-exposure prophylaxis.

^b^ART: antiretroviral therapy.

^c^PLW: pregnant and lactating women.

^d^IDI: in-depth interview.

^e^SOP: standard operating procedure.

^f^MM+: Mentor Mothers Plus.

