#### Descriptive Analysis and Effectiveness Outcomes

We will use basic measures (proportions, means and SDs, medians and IQRs, as appropriate) and graphical displays to describe distributions of key variables. Bivariable analyses will use Student's *t* tests (replaced by Mann-Whitney U tests for nonnormal distributions) or chi-square tests (replaced by exact tests for sparse data), as appropriate. We will compare study arms’ descriptive statistics without tests of statistical significance. Comparisons of randomized groups’ primary analyses will be by intention to treat, with secondary analyses based on intervention uptake. Specifically, we will evaluate reductions in alcohol use from baseline to 6-month follow-up in PEth levels, with confirmation of self-reported AUDIT-C scores compared by study arm. For secondary HIV outcomes, we will evaluate ART and PrEP adherence by study arm using urine TFV levels for recent adherence and VLs at 6 months for women on ART.

All statistical tests will be two-sided at α=.05; all effect estimates will be reported with 95% CIs. For both aims, we propose a priori subgroup analyses by age and HIV status. For subgroup analyses, effect modification will be assessed from the fully adjusted model on the additive scale by calculating the relative excess risk due to interaction [54] and on the multiplicative scale by examining the interaction term in regression models. Data will be analyzed in Stata version 15.

We will track missing variables in our monthly quality control and follow-up on all missing exposures and outcomes at each visit. We will conduct sensitivity analyses, including multiple imputation, to include evaluation outcomes and exposures from missing data and incomplete retention. Our retention efforts will focus on retention in both groups to ensure that there is no differential loss to follow-up. Analysis of implementation outcomes will entail descriptive summarization of acceptability, feasibility, and fidelity of MM+, including for women of different socioeconomic statuses or education levels.

Data management procedures will be developed with the statistical analysis plan and available upon demand to study investigators.

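### The >80% power claim holds only if control reduction is about 2.5% or less (percentages read as shares of women), and no power is defined for feasibility

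*Protocol article*

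**What the plan says.** The Power Calculations section of the protocol article bases power on a "20% or more reduction in alcohol use in the intervention arm compared to no reduction (or minimal <5% reduction) in the control group". It sets the size at 100 women, 50 per arm, and concludes that "our study will be adequately powered at >80% for all primary effectiveness outcomes of feasibility and reduction in alcohol use". It does not state the scale of the percentages, an SD, a baseline rate or the test used.

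Other sections bear on this:

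- Descriptive Analysis and Effectiveness Outcomes fixes the error rate: "All statistical tests will be two-sided at α=.05". It replaces chi-square tests with exact tests when data are sparse, and limits the implementation outcomes to descriptive summary.
- RCT Outcomes defines the primary outcome as the change in alcohol use from baseline to 6 months, measured by PEth.
- The feasibility row of Table 2 reads "Evaluate organizational, provider, and PLW views on the feasibility and scalability of the implementation of the intervention". It has no numeric target, whereas acceptability and fidelity each have a success threshold above 80%.
- The Abstract lists feasibility among the secondary outcomes. The Outcomes part of the Analysis Plan lists it as an implementation outcome.

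**The concern.** The paragraph makes one unqualified power statement for a range of control assumptions and for two outcomes. Power to separate 20% from a few per cent changes quickly with the control rate when there are 50 per arm, so a figure that is right at one end of the range need not be right at the other. A power figure also needs a hypothesis, a threshold and a test, and feasibility has none of these.

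What is at stake is how a null alcohol result would be read. If the trial is described as adequately powered, a non-significant difference looks like evidence against MM+. If power could be nearer 60%, it is not. The Abstract's conclusion that the RCT will evaluate efficacy adds to that risk.

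**Working it through.** **Inputs.** 50 per arm, MM+ reduction 20% (the stated minimum) and control reduction from 0% to just under 5%, all from Power Calculations. Two-sided alpha .05 from Descriptive Analysis and Effectiveness Outcomes.

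**1. Percentages read as shares of women.** With p1 = 0.20, control share p2 and p̄ = (p1 + p2)/2:

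power = Φ{ [ (p1 − p2)√n − 1.96·√(2p̄(1 − p̄)) ] / √(p1(1 − p1) + p2(1 − p2)) }

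- Control 0%, where the plan's figure is reproduced: (0.20 × 7.071 − 1.96 × 0.4243)/0.400 = (1.414 − 0.832)/0.400 = 1.457, so power is 92.7%.
- Control 2.5%: (0.175 × 7.071 − 1.96 × 0.4469)/0.4294 = (1.237 − 0.876)/0.4294 = 0.842, so power is 80.0%.
- Control 5%: (0.15 × 7.071 − 1.96 × 0.4677)/0.4555 = (1.061 − 0.917)/0.4555 = 0.316, so power is 62.4%.

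| Control reduction | Pooled, 50/arm | Fisher exact, 50/arm | Pooled, 40/arm (assumed) |
|---|---|---|---|
| 0% | 92.7% | 95.2% | 86.0% |
| 1% | 88.5% | – | 80.3% |
| 2% | 83.1% | 77.9% | 73.9% |
| 3% | 76.8% | – | 67.0% |
| 4% | 69.8% | – | 59.9% |
| 5% | 62.4% | 50.8% | 52.8% |

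Other methods at 20% versus 5% give 64.4% (unpooled), 66.3% (arcsine) and 66.4% (exact enumeration of the chi-square test). Even one-sided tests reach at most 76.9%. The Fisher column is relevant because a control share of 2–5% of 50 women is 1 to 2.5 expected events, which is sparse. With Fisher's test, 80% power is kept only up to about 1.7% in control.

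For 80% power at 20% versus 5%, the pooled formula needs 76 per arm. With 50 per arm the detectable contrast is about 25% versus 5%: (0.20 × 7.071 − 1.96 × 0.5050)/0.4848 = 0.876, power 81%. With 40 evaluable per arm it is about 28% versus 5%: (0.23 × 6.325 − 1.96 × 0.5249)/0.4991 = 0.853, power 80%. The 40 per arm is an assumption; the article gives no retention figure.

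**2. Percentages read as a relative fall in PEth level.** On the log scale the difference is ln(1/0.80) = 0.223 against no control change, and ln(0.95/0.80) = 0.172 against a 5% fall. The largest SD that keeps 80% power is roughly difference/[(1.96 + 0.842)√(2/50)] = difference/0.560. That gives 0.398 and 0.307, or 0.394 and 0.304 with the noncentral t. Over assumed SDs, the normal approximation gives:

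| Log-scale SD (assumed) | 20% vs 0% | 20% vs 5% |
|---|---|---|
| 0.3 | 96% | 82% |
| 0.5 | 61% | 41% |
| 1.0 | 20% | 14% |

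**3. Feasibility.** Power Calculations treats it as a primary effectiveness outcome. The Abstract makes it secondary, and the Analysis Plan makes it an implementation outcome. Table 2 gives no threshold, and the analysis is descriptive. There is no null value, alternative or test to put into a power formula. Precision can be given instead for an implementation proportion: at 80% with n = 50, the half-width is 1.96 × √(0.8 × 0.2/50) = 0.111, about ±11 points.

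**The case against.** The strongest reply is that the control assumption named first is no reduction at all. There the claim is correct on the proportion reading, with about 93% power. The 62% pairs the minimum MM+ effect with the excluded upper edge of the control range. A reader might infer that the trial simply has 62% power; the documents do not support that. They support a range, and they do not say that the percentages are shares of women. This part of the objection stands and sets the form of the point. It does not rescue the sentence, which claims more than 80% without qualification for the whole stated range.

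A reader might also infer that Background contradicts the small control change, since it says that "interventions such as the Philani Program Plus (an MM model) have shown reduction in alcohol use over extended periods". It does not. That sentence concerns extended periods and goes on to say that early abstinence is hard to achieve. Study Design for the Pilot RCT says the control counselling carries no alcohol messaging. A small control change over 6 months is arguable, not refuted.

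Three further limits stand:

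- The PEth reading depends on an SD that the article does not give, so it yields a condition and not a verdict of low power.
- A missing attrition allowance may sit in the full protocol, so it is not counted as an error here; 40 per arm only illustrates sensitivity.
- It would be too strong to say feasibility can never be powered. With a numeric criterion it could be; as specified, it is not.

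Finally, the trial is called a pilot with preliminary effectiveness, and 95% CIs are promised for all effect estimates. That lessens the harm but leaves the power sentence as it is.

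**Conclusion.** The power statement is wrong as written, in two limited respects.

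First, on the proportion reading with all 100 women analysed, power runs from about 93% at 0% control reduction to about 62% at 5% (51% with Fisher's test). It crosses 80% at about 2.5%, so the claim fails over about the upper half of the plan's own range. On a relative-PEth reading it holds only if the log-scale SD is at most about 0.39 (against 0%) or 0.30 (against 5%), which cannot be checked from the article.

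Second, no power is defined for feasibility as specified, and calling it a primary effectiveness outcome conflicts with the Abstract and the Analysis Plan. This second part rests on no numerical assumption.

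**What to change.** Rewrite the power paragraph:

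- State whether the percentages are shares of women or changes in PEth level, matching the primary analysis. If PEth change, give the assumed SD.
- Replace the single figure with the range over the stated control assumption (if proportions, about 93% at 0% to 62% at 5%), or with the detectable difference: 25% versus 5% with 50 per arm, or about 28% versus 5% if 40 per arm are evaluable, with that number labelled as an assumption.
- Remove feasibility from the power sentence, and give the expected CI precision for implementation proportions (about ±11 points at 80% with n = 50).

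The cost is one reworded paragraph and a less favourable stated figure. No extra participants are needed.

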#### Qualitative Data Analysis

We will transcribe, translate, and import postintervention qualitative data into a software package, and a team of three researchers with expertise in qualitative research methods will code the data using a hybrid inductive-deductive approach. We will measure interrater reliability to ensure consistent code application between interviewers; this process will be iterative, and code definitions will be refined until application is consistent across coders. We will develop code summaries and memos for emerging themes using an experienced trained team of qualitative researchers from the HSRC and the San Diego State University (SDSU), who will use open coding to analyze segments of the data, create focused codes, and highlight quotable text. We will use a deductive approach from our theoretical framework on individual-, facility-, and HIV-level facilitators of alcohol reduction or abstinence and PrEP or ART continuation and adherence, allowing inductive codes to emerge. We will use a thematic analysis allowing key issues to emerge from the data. Multiple data sources (participants, providers) will be triangulated to provide a holistic understanding of the intervention acceptability [52]. We will use the COREQ (Consolidated Criteria for Reporting Qualitative Research) checklist to ensure positionality, reflexivity, etc, are covered to ensure rigor [53].

#### Descriptive Analysis and Effectiveness Outcomes

We will use basic measures (proportions, means and SDs, medians and IQRs, as appropriate) and graphical displays to describe distributions of key variables. Bivariable analyses will use Student's *t* tests (replaced by Mann-Whitney U tests for nonnormal distributions) or chi-square tests (replaced by exact tests for sparse data), as appropriate. We will compare study arms’ descriptive statistics without tests of statistical significance. Comparisons of randomized groups’ primary analyses will be by intention to treat, with secondary analyses based on intervention uptake. Specifically, we will evaluate reductions in alcohol use from baseline to 6-month follow-up in PEth levels, with confirmation of self-reported AUDIT-C scores compared by study arm. For secondary HIV outcomes, we will evaluate ART and PrEP adherence by study arm using urine TFV levels for recent adherence and VLs at 6 months for women on ART.

All statistical tests will be two-sided at α=.05; all effect estimates will be reported with 95% CIs. For both aims, we propose a priori subgroup analyses by age and HIV status. For subgroup analyses, effect modification will be assessed from the fully adjusted model on the additive scale by calculating the relative excess risk due to interaction [54] and on the multiplicative scale by examining the interaction term in regression models. Data will be analyzed in Stata version 15.

We will track missing variables in our monthly quality control and follow-up on all missing exposures and outcomes at each visit. We will conduct sensitivity analyses, including multiple imputation, to include evaluation outcomes and exposures from missing data and incomplete retention. Our retention efforts will focus on retention in both groups to ensure that there is no differential loss to follow-up. Analysis of implementation outcomes will entail descriptive summarization of acceptability, feasibility, and fidelity of MM+, including for women of different socioeconomic statuses or education levels.

Data management procedures will be developed with the statistical analysis plan and available upon demand to study investigators.

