#### RCT Outcomes

The RCT primary outcome is the preliminary effectiveness (comparing the MM+ arm to the enhanced HIV attention control arm using intention-to-treat analysis) defined as a reduction in alcohol use via biomarker-confirmed self-reported and biological samples (comparing baseline to 6 months in phosphatidylethanol [PEth] blood samples).

Secondary outcomes include (1) PrEP initiation and adherence (via patient records and urine TFV testing at 6 months) and (2) ART adherence (via urine TFV testing and self-report). In addition, we will evaluate three of the eight implementation outcomes, as defined by Proctor et al [46]: feasibility, acceptability (including participant satisfaction with the intervention), and fidelity. We will also track any social or health harms in the study and relatedness to the study intervention through study surveys and review of medical records. Table 2 describes how these outcomes will be measured. We will track session attendance, as well as ART and PrEP adherence, at each study visit.

**Table 2 table2:** Description of aim 3 implementation outcomes.

Evaluation parameter	Description	Methods	Frequency
Theoretical model	Evaluate changes in alcohol use and HIV prevention or treatment (eg, PrEP^a^ and ART^b^ use) using the theory-of-change model measuring change and which sociodemographic and behavioral characteristics are associated with change in order to understand any subpopulations receptive toward the strategic priorities and pathways of change identified by our model.	Quantitative surveys at each visit and biomarker data	Baseline and 6-month follow-up
Participants’ self-reported fidelity	Evaluate completeness of the intervention through a checklist assessing whether specific topics were covered during intervention sessions, including an assessment of the quality of intervention interactions, where participants will rate implementer engagement during intervention sessions.	Quantitative surveys at each visit and biomarker data	Baseline and 6-month follow-up

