#### Outcome Data Ascertainment

Participants will be followed for 6 months. During this time, they will have three study visits, in which they will self-report alcohol use and PrEP or ART initiation or continuation to study staff. At each study visit, we will ascertain dried blood spots for assessment of recent alcohol use, via PEth testing (PEth<20 ng/mL represents light or no consumption [47]) and AUDIT-C, a validated survey of alcohol use (0=abstinence, >0=recent alcohol use). Participant medical files will be reviewed at the end of the study to ascertain birth outcomes (including any pregnancy loss or stillbirth), reported harms, and PrEP and ART prescription. At each study visit, participants will provide a urine sample to the study staff for analysis of recent PrEP or ART use using urine TFV testing (of recent adherence in the past 72 hours). Urine TFV results will show recent adherence and will be evaluated in conjunction with viral loads (VLs). For those on ART, we will review their files for VLs to evaluate VL suppression at baseline and end of the trial (VL<200 copies/mL). If VLs are unavailable, we will track them online with the national health laboratory service.

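### The primary outcome is framed as change in PEth with only t or Mann-Whitney tests named; read as written, the primary contrast gives up the precision of adjusting for baseline PEth

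*Protocol article*

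**What the plan says.** The RCT Outcomes section of the protocol article defines the primary outcome as a reduction in alcohol use, "comparing baseline to 6 months in phosphatidylethanol [PEth] blood samples". The section Descriptive Analysis and Effectiveness Outcomes repeats this: "we will evaluate reductions in alcohol use from baseline to 6-month follow-up in PEth levels", by study arm, supported by AUDIT-C. It adds that "primary analyses will be by intention to treat, with secondary analyses based on intervention uptake".

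The tests named there for bivariable work are Student's t tests, "replaced by Mann-Whitney U tests for nonnormal distributions", and chi-square tests, with exact tests for sparse data. The section rules out significance testing of the arms' descriptive statistics. It also says "All statistical tests will be two-sided at α=.05; all effect estimates will be reported with 95% CIs".

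Adjustment is mentioned once, for the subgroup analyses by age and HIV status: "effect modification will be assessed from the fully adjusted model on the additive scale". No covariates are listed, and baseline PEth is not named as a covariate for any analysis. Outcome Data Ascertainment gives a cut-off, "PEth<20 ng/mL represents light or no consumption", but does not make it the primary endpoint.

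**The concern.** The outcome is framed as a change from baseline, and descriptive arm comparisons are to be made without tests. The natural use left for the t and Mann-Whitney tests is therefore the outcome comparison. Followed literally, the primary result would be an unadjusted two-sample test of change in PEth.

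Subtracting baseline assumes that a woman's 6-month value moves one for one with her baseline value. When the correlation between the two is moderate, subtraction brings in baseline noise that the follow-up value does not share. With 100 women, that lost precision goes straight into the width of the interval for the arm effect, which is what a later, larger trial would rely on. Baseline PEth has to be measured for the change score anyway, so a better use of it costs nothing in the field.

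**Working it through.** **Inputs.** From the article: 50 women per arm, 1:1, two-sided alpha 0.05, PEth at baseline and 6 months. Not in the article, so assumed: the baseline-to-6-month correlation rho, the SD of log PEth, and the effect size in SD units.

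**The plan's own figure.** Power Calculations claims more than 80% power for "20% or more reduction in alcohol use in the intervention arm compared to no reduction (or minimal <5% reduction) in the control group". It names no scale, SD or model, so the claim cannot be tied to one analysis:
- As proportions of women who reduce, 20% against 0% gives 92.7% power and 20% against 5% gives 62.4%.
- As a 20% fall in geometric mean PEth against none, the detectable difference at 80% power is (1.960 + 0.842) × sqrt(2/50) = 0.560 SD. The SD of the analysed log quantity would have to be 0.223/0.560 = 0.40.

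The present point does not depend on that figure.

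**Variance of the arm difference**, in units of an analysis of the 6-month value alone, with equal variances at both times:
- change score: 2(1 − rho)
- ANCOVA: 1 − rho²
- ratio, ANCOVA to change: (1 − rho²) / [2(1 − rho)] = (1 + rho)/2

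| rho (assumed) | Change score | ANCOVA | Ratio | Power of ANCOVA if the change score had 80% | Women per arm for 80% with ANCOVA |
|---|---|---|---|---|---|
| 0.3 | 1.40 | 0.91 | 0.65 | 93.5% | 33 |
| 0.5 | 1.00 | 0.75 | 0.75 | 89.9% | 38 |
| 0.7 | 0.60 | 0.51 | 0.85 | 86.0% | 43 |
| 0.9 | 0.20 | 0.19 | 0.95 | 82.0% | 48 |

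Below rho = 0.5 the change score has a variance above 1, so it is less precise than ignoring baseline altogether.

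**Unequal variances.** With SDs s0 at baseline and s1 at 6 months, change variance minus ANCOVA variance is (s0² + s1² − 2·rho·s0·s1) − s1²(1 − rho²) = (s0 − rho·s1)². This is never negative, so the direction of the result does not rest on equal variances; only its size does.

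**Power at one assumed effect**, 0.5 SD with 50 per arm, from Phi(0.5 / [sqrt(V) × 0.2] − 1.96), where V is the variance in the table and 0.2 = sqrt(2/50):
- rho = 0.3: change 56%, ANCOVA 75%
- rho = 0.5: change 70%, ANCOVA 82%
- rho = 0.7: change 90%, ANCOVA 94%

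If the log SD were 1, 0.5 SD would be a geometric mean ratio of exp(−0.5) = 0.61. That is a larger fall than the 20% used for planning, so these powers illustrate the comparison of methods and do not forecast the trial's power.

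**Choosing the test by distribution.** In 2,000 simulated trials per setting (lognormal PEth, log SD 1, 50 per arm, 0.5 SD effect), a normality test on raw change decided between t and Mann-Whitney:

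| rho | t or Mann-Whitney on raw change | t test on log change | ANCOVA on log PEth |
|---|---|---|---|
| 0.3 | 44% | 57% | 75% |
| 0.5 | 52% | 70% | 81% |
| 0.7 | 72% | 88% | 93% |

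With no true effect, the test chosen by distribution rejected in 4.5% to 4.8% of trials, so type I error was not inflated. The loss is in power. Part of it comes from the raw scale and part from not adjusting for baseline.

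**The case against.** The strongest reply is that the article does not commit to an unadjusted test. The t and Mann-Whitney sentence concerns bivariable analyses and follows the descriptive statistics. The primary-outcome sentence names no test and no model, and the same section mentions regression and a fully adjusted model. A separate statistical analysis plan is referred to and not shown, and the exact model is something an article commonly leaves to it.

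This stands in part. The unadjusted reading is an inference, and the unseen plan may already settle the matter. However, the adjusted model is tied to subgroup effect modification only. For the primary contrast, the text fixes a change-from-baseline outcome and offers no method beyond the two-sample tests.

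A second reply is that the outcome may be binary. The relative excess risk due to interaction belongs to a risk model, a 20 ng/mL cut-off is given, and the planned 20% reduction has no stated scale. On a binary endpoint the (1 + rho)/2 ratio does not apply. That limits the arithmetic to the continuous reading, which is the one suggested by the references to PEth levels.

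A reader might also infer several stronger claims that the documents do not support:
- That baseline PEth is thrown away. It is used, with a fixed coefficient of 1.
- That switching tests is itself invalid. The article describes no formal pretest, and type I error held in simulation.
- That Mann-Whitney conflicts with the promise of confidence intervals. A Hodges-Lehmann shift with its interval can accompany it.
- That baseline adjustment cures a floor effect. Entry rests on self-reported drinking with no PEth threshold, so some women may start near the floor. The covariate does not give them room to fall, and their number is unknown.

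**Conclusion.** The concern holds in a limited form. Read as written, the primary contrast is an unadjusted comparison of change in PEth, and adjusting for baseline would be more precise at no cost in data. On a continuous scale with equal variances, the variance saving is 35% at rho = 0.3, 25% at 0.5, 15% at 0.7 and 5% at 0.9. It is substantial at low to moderate correlation and small at high correlation. The documents do not give rho, so the actual gain is unknown.

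This is a matter of efficiency and of fixing one estimator in advance. It is not a matter of bias or of a false type I error rate. Confidence is high in the statistical ordering of the two methods and moderate in the reading of which test is intended. The change should be made, though the pilot does not stand or fall on it.

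**What to change.** State one primary model in the analysis section: linear regression of log PEth at 6 months on arm, with baseline log PEth as covariate, in all women as randomised. Fix in advance how values below the assay limit are handled, either by a set substitution value or by a censored model. Report the geometric mean ratio between arms with its 95% CI.

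Keep the rank test (with a Hodges-Lehmann interval if an estimate is wanted) and the proportion with PEth below 20 ng/mL as sensitivity analyses. The choice of primary method then no longer depends on the observed distribution.

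The cost is a few lines of analysis text and one degree of freedom, with no added visits, samples or participants. If the statistical analysis plan already specifies baseline adjustment, bring the article's wording into line with it.
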